## Abstract

**Background:**

Low levels of serum selenium are associated with increased risk of mortality among HIV+ patients in East Africa. We aim to assess the effect of selenium supplementation on CD4 cell count, HIV viral load, opportunistic infections, and quality of life in HIV-infected patients in Rwanda.

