### Objectives and Hypothesis

The primary outcome of the study is time from baseline to reduction of CD4 T lymphocyte count below 350 cells/mm^3^ (confirmed by two measures at least one week apart), or start of ART, or the emergence of a documented CDC-defined AIDS-defining illness. We hypothesize that selenium supplementation in pre-ART patients will improve CD4 cell counts, decrease opportunistic infections, decrease HIV viral load, and delay ART initiation.

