### Setting and Participants

Patients will be recruited at two purposely-selected health facilities that offer care and treatment for HIV/AIDS patients in Rwanda. These facilities have been chosen due to the feasibility of recruiting all patients within a 3-4 month period and the feasibility of coordination.

Patient eligibility will be restricted to HIV-infected adults 21 years of age and older at study enrolment. Only patients not yet eligible for ART will be included. Only patients with CD4 cell count between 400 and 650 cells/mm^3 ^will be selected because they are at similar immunological level and hence they will not be eligible to start ART treatment at the start of the study. Eligible participants must also be willing to practice a barrier method of birth control at all times. Written informed consent will be required from patients to participate in this study.

Eligible patients will be identified from patient registers. These patients will be informed about the study during a regular scheduled clinic visit or through home visits by site staff not otherwise involved in data collection. Patients who are interested in the study will be provided with further details and consent procedures. Those fitting the inclusion criteria will be enrolled and followed for 2 years. Study assessments will occur at baseline, 6, 12, 18, and 24 months.

Patients will be excluded if they are intending to be transferred out of the clinic catchment area before study ends and/or if they are scheduled to start ART. Moribund patients, pregnant women, and those unable or not wanting to commit to barrier method of birth control will also be excluded.

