### Measurement of Outcomes and Other Variables of Interest

#### Patient Interviews

Trained nurses will use a structured questionnaire to collect data on patients' demographics at baseline. Additionally, at baseline and at each follow-up visit, a questionnaire will be used to collect information on psychosocial factors, access to care and treatment, attitudes towards and experiences with the supplementation, quality of life, self-efficacy, nutrition, opportunistic infections, and adherence to the study protocol. The questionnaire will be available in English and Kinyarwanda. Nurses will also use a data abstraction tool at baseline and at each follow-up visit to obtain information on height, weight, blood pressure and other clinically relevant information.

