#### HIV Viral Load and CD4 Cell Count

At baseline, and at month 6, 12, 18 and 24, blood draws will be done for assessment of CD4 cell count and HIV viral load. Blood samples will be collected into EDTA tubes (Becton Dickinson, San Jose, CA, USA). The viral load samples will be transported and analyzed at the National Reference Laboratory within 4 hours; plasma will be separated from cells by centrifugation at 200 g, aliquoted and stored at -70°C until the real time PCR will be performed using Cobas TaqMan 48 (Roche Diagnostic Systems, NJ, USA) that has a detection limit of 40 RNA copies/ml. The RNA will be extracted from the plasma with chloroform, followed by alcohol precipitation and dilution with the HIV Monitor specimen diluent (100 μl). Amplification and detection of the extracted RNA (40 μl) will be performed in accordance with the manufacturer's instructions. CD4 cell count will be measured at the National Reference Lab, or the site laboratory, using FACS Count (Becton Dickinson immunocytometry).

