### Analysis Plan

Analysis will be conducted jointly by the study team in Rwanda and in Canada using standard statistical software. The analysis and reporting of the results with follow the CONSORT guidelines [38]. The statistician/data analyst will be blinded to the study group. The process of patient selection and flow throughout the study will be summarized using a flow-diagram (See Figure 1). The analysis results of patient demographics and baseline outcome variables (both primary and secondary) will be summarized using descriptive summary measures: expressed as mean (standard deviation) or median (minimum-maximum) for continuous variables and number (percent) for categorical variables. We will adopt an intention-to-treat principle to analyze all outcomes, meaning that data from participants will be analyzed according to the group to which they were randomized even if they do not receive the allocated intervention. We will also use multiple-imputation to handle missing data. We will use the T-test for comparing groups on continuous outcomes and the chi-squared test for binary outcomes. We will consider a threshold of 0.05 as statistical significance. For all group comparisons, the results will be expressed as effect (risk ratio for binary outcomes), corresponding two-sided 95% confidence intervals and associated p-values. P-values will be reported to three decimal places with values less than 0.001 reported as < 0.001. Because the primary outcome is a composite outcome, we will assess heterogeneity between the included outcomes [39,40]. Further, adjusted analyses using the following baseline covariates (age, gender, nutritional status) will be performed using regression techniques to investigate the residual impact of key baseline characteristics on the outcomes. Goodness-of-fit will be assessed by examining the residuals for model assumptions and chi-squared test of goodness-of-fit. All analyses will be performed by a professional statistician.

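### Continuous outcomes are compared by a T-test that leaves out the baseline value and the repeated visits, and CD4 count, a stated aim, is not listed as a continuous outcome

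*Protocol article*

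**What the plan says.** **Method.** The Analysis Plan section of the protocol article says: "We will use the T-test for comparing groups on continuous outcomes", with the chi-squared test for binary ones. It names no visit for the continuous comparisons. It then adds that "adjusted analyses using the following baseline covariates (age, gender, nutritional status) will be performed using regression techniques". The baseline value of the outcome is not among those covariates.

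**Data.** Under Setting and Participants: "Study assessments will occur at baseline, 6, 12, 18, and 24 months". The laboratory section says that at these same times "blood draws will be done for assessment of CD4 cell count and HIV viral load". The Patient Interviews section says that "at baseline and at each follow-up visit, a questionnaire will be used to collect information on psychosocial factors"; the same sentence goes on to list quality of life, and weight is abstracted at the same visits.

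**Aim against outcome list.** The abstract opens its aim with CD4: "We aim to assess the effect of selenium supplementation on CD4 cell count, HIV viral load, opportunistic infections, and quality of life". The closing paragraph of the Background likewise gives the effect on CD4 counts as the reason for the design. The hypothesis is that "selenium supplementation in pre-ART patients will improve CD4 cell counts". In the Outcomes section, CD4 appears only as a confirmed fall below 350 cells/mm³, one of three components of the primary composite. The secondary outcomes are viral suppression at the four visits, quality of life, weight gain, opportunistic infections and mortality.

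**The concern.** There are two separate points.

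1. A two-group T-test takes one number per patient. When a baseline and four follow-up values exist, it leaves unused the baseline value, usually the best single predictor of follow-up, and all visits but one. The cost is wider confidence intervals for the secondary outcomes in a trial whose size, by its own account, was set partly by resources. Because no visit is named, the estimate to be reported is also left open.

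2. The aim and hypothesis concern CD4 count, but no listed outcome measures its level, change or slope. A composite that also counts ART start and AIDS-defining illness, and that reduces CD4 to a threshold, answers a related but different question. A reader of the final report could not tell which CD4 analysis, if any, had been planned to test the hypothesis.

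**Working it through.** The article gives no standard deviation, effect size or correlation for any continuous outcome, so there is no stated figure to reproduce. The calculation below shows only relative efficiency.

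**Inputs**
- Total sample 300 (Sample Size Calculation). The allocation ratio is not stated; 1:1, hence 150 per arm, is assumed.
- Two-sided 0.05 (Analysis Plan).
- 80% power is used as a reference point. The article applies it only to the event rate.
- ρ, the correlation between baseline and follow-up, is assumed: 0.3, 0.5, 0.7. Equal variance at baseline and follow-up is also assumed.

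**Formulas**, with the variance of a follow-up T-test at one visit set to 1:
- ANCOVA on baseline: 1 − ρ²
- T-test on change from baseline: 2(1 − ρ)
- Follow-up T-test against ANCOVA: 1/(1 − ρ²)
- Change-score T-test against ANCOVA: 2(1 − ρ)/(1 − ρ²) = 2/(1 + ρ)

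| ρ (assumed) | ANCOVA variance | Change-score variance | Follow-up T-test ÷ ANCOVA | Change-score T-test ÷ ANCOVA |
|---|---|---|---|---|
| 0.3 | 0.91 | 1.40 | 1/0.91 = 1.10 | 2/1.3 = 1.54 |
| 0.5 | 0.75 | 1.00 | 1/0.75 = 1.33 | 2/1.5 = 1.33 |
| 0.7 | 0.51 | 0.60 | 1/0.51 = 1.96 | 2/1.7 = 1.18 |

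The fourth column applies to an outcome compared on follow-up values, as quality of life might be. The last column applies to weight gain if it is read as a change score.

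**In terms of power.** With 150 per arm, the smallest difference a T-test at one visit detects with 80% power is (1.960 + 0.842) × √(2/150) = 0.323 SD. Multiplying by √(1 − ρ²) gives the figure for ANCOVA: 0.309, 0.280 and 0.231 SD at ρ = 0.3, 0.5 and 0.7. For a true difference of 0.323 SD, ANCOVA has power 83.6%, 89.9% and 97.5%. Equivalently, the precision of 300 patients by T-test could be had from 300 × (1 − ρ²) = 273, 225 or 153 patients.

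**Using all visits.** If the mean of the four follow-up visits is the target, with baseline adjustment and equal correlation between all visits, the relative variance is (1 + 3ρ)/4 − ρ² = 0.385, 0.375 and 0.285. This is a different quantity from the effect at one visit, so it shows what the extra visits can contribute and is not a like-for-like saving.

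**CD4, by comparison of sections.** The aim (abstract), the purpose of the design (Background) and the hypothesis (Objectives and Hypothesis) all name CD4 count. The Outcomes section has it only as the below-350 component, and the secondary list does not contain it. The count is nevertheless drawn at all five time points. The mismatch therefore lies in the outcome list, not in data collection.

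**The case against.** Several objections have force.

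- *The T-test is valid.* This stands. Under randomization it is unbiased; the point is efficiency and an unnamed visit.
- *A condensed article leaves modelling to the analysis plan.* This stands in part. Covariance structure and model terms can wait. But the article does name a method, and what it names omits baseline and repeated measures. The gap between aims and outcomes lies wholly within the article.
- *Other models are planned.* The adjusted regressions do not list the baseline outcome. Nutritional status might include baseline weight, but the article does not say so. The abstract mentions stepwise regression and structural equation modeling; the Analysis Plan does not, and neither is tied to baseline values or repeated visits. They do not close the gap.
- *Weight gain already uses baseline.* This stands, and is why it has its own, different ratio.
- *The correlations are assumed.* This stands. For CD4, entry limited to 400–650 cells/mm³ would tend to lower ρ, towards the small gain of 1.10.

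A reader might also infer more than the documents support:

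- *Four T-tests per outcome, with inflated false positives.* The Analysis Plan names no visit. Only viral suppression is tied to the four visits, and it is binary, so it falls under the chi-squared test. No multiplicity figure can be attached to the continuous outcomes.
- *Distortion of the existing plan by CD4 rises after ART start.* No continuous CD4 analysis is listed, so there is none to distort. The issue arises only once such an outcome is added.
- *Viral load mishandled by T-test.* It is listed only as suppression.
- *No analysis of CD4 at all.* Too strong: confirmed decline below 350 is a primary component, and heterogeneity between components is to be assessed. What is missing is a continuous outcome.

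**Conclusion.** Both parts hold, in limited form. The stated T-test is valid but inefficient. Over assumed correlations of 0.3 to 0.7, its variance is 1.10 to 1.96 times that of a baseline-adjusted comparison for outcomes taken at follow-up, and 1.54 down to 1.18 times for weight gain as a change score. These ratios rest on the assumed correlations and on equal variances; the power figures also assume 1:1 allocation. Independently of any assumption, CD4 count is a stated aim and hypothesis without a matching continuous outcome. The primary composite and its sample size are untouched. This is worth changing because it costs almost nothing, not because the planned comparisons would mislead.

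**What to change.** 1. In the Analysis Plan, replace the T-test for continuous outcomes with a linear mixed model that uses all visits and adjusts for the baseline value, or with ANCOVA at one named visit. Prespecify one contrast per outcome.
2. Add CD4 count, as change or slope, to the secondary outcomes and analyse it in the same way. State how values after ART start are handled in the analysis, and add a sensitivity analysis using all values. Both are needed because cutting the series at ART start removes values for a reason that may depend on CD4 itself.
3. State whether weight gain is analysed as a change score or as follow-up weight adjusted for baseline.

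Cost: wording in the Outcomes and Analysis Plan sections and slightly more modelling. Every measurement needed is already scheduled; no visits, blood draws or patients are added.

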**Methods and Design:**

A 24-month, multi-centre, patient and provider-blinded, randomized, placebo-controlled clinical trial involving 300 pre-antiretroviral therapy (ART) HIV-infected patients will be carried out at two sites in Rwanda. Patients ≥ 21 years of age with documented HIV infection, CD4 cell count of 400-650 cells/mm^3^, and not yet on ART will be recruited. Patients will be randomized at each study site using a randomized block design to receive either the selenium micronutrient supplement or an identically appearing placebo taken once daily. The primary outcome is a composite of time from baseline to reduction of CD4 T lymphocyte count below 350 cells/mm^3^ (confirmed by two measures at least one week apart), or start of ART, or the emergence of a documented CDC-defined AIDS-defining illness. An intention-to-treat analysis will be conducted using stepwise regression and structural equation modeling.

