### Randomization

Participants will be randomized using a simple randomized block design to receive either selenium or an identically appearing placebo to be taken once daily for 24 months. The Rwandan Ministry of Health recommends the use of co-trimoxazole, a sulfonamide antibiotic combination of trimethoprium and sulfamethoxazole used for the treatment of a variety of bacterial infections, for all HIV-infected patients. Therefore, all participants will also receive co-trimoxazole irrespective of experimental assignment. Participants who do not return to the clinic as scheduled will be followed up at home.

Study participants will be identified by a unique study identification number. The randomization schedule will be prepared by the product manufacturer, Seroyal, and the randomization sequence will be concealed from the study investigators and providers. Study participants will be assigned a specific allocation number. An unblinding list will be kept at the site of the manufacturer and will be provided as needed to the Data and Safety Monitoring Officer (DS). Site study personnel (investigator and clinical personnel monitoring the safety and laboratory assay results) and study participants will be blinded with respect to the allocation. Unblinding of an individual study participant will be indicated in the event of a medical emergency where the clinical management/medical treatment of the study participant could be altered by knowledge of the group assignment allocation of the investigational product.

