### Outcomes

The primary outcome of the study is a composite outcome involving reduction of CD4 T lymphocyte count to below 350 cells/mm^3^ (confirmed by two measures at least one week apart), or start of ART, or the emergence of a documented CDC-defined AIDS-defining illness. Secondary outcomes includes viral suppression at 6, 12, 18, and 24 months; quality of life; weight gain; presence of opportunistic infections and mortality.

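### Baseline CD4 is measured on everyone and sets the distance to the 350 threshold, yet neither the main tests nor the adjusted analysis uses it: a modest, nearly free gain in power is left unused.

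*Protocol article*

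**What the plan says.** The Analysis Plan section gives the group comparisons as "We will use the T-test for comparing groups on continuous outcomes and the chi-squared test for binary outcomes", with a risk ratio as the effect measure for binary outcomes. It then adds that "adjusted analyses using the following baseline covariates (age, gender, nutritional status) will be performed using regression techniques", with the stated aim "to investigate the residual impact of key baseline characteristics on the outcomes". The list names three covariates. Neither baseline CD4 nor site is among them.

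Elsewhere in the article:

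- **Outcomes:** the primary outcome is a "composite outcome involving reduction of CD4 T lymphocyte count to below 350" cells, or start of ART, or an AIDS-defining illness.
- **Setting and Participants:** "Only patients with CD4 cell count between 400 and 650" cells are eligible.
- **HIV Viral Load and CD4 Cell Count:** at baseline and every six months, "blood draws will be done for assessment of CD4 cell count and HIV viral load".
- **Abstract, Methods and Design:** "Patients will be randomized at each study site using a randomized block design". The Randomization section says only "Participants will be randomized using a simple randomized block design" and does not mention site.

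The abstract also mentions stepwise regression and structural equation modelling. It names no covariates for either, so it does not supply the missing one.

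**The concern.** The outcome is the crossing of a fixed line, and entry CD4 is each patient's starting distance from that line. The eligibility window alone makes this distance vary sixfold. The sample size section itself ties one-year risk to entry CD4 when it expects about 60% of patients to enter at a level from which 350 is within reach in a year.

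A strong predictor left out of the analysis stays in the residual variation of the treatment comparison. The trial has little power to spare: Table 1 asks for 314 patients for the 25% reduction and the plan enrols 300. Because the article names its covariates, this is a choice that it has made, not a detail left to an analysis plan.

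**Working it through.** **1. The plan's own figure.** Table 1 gives N = 314 for 60% versus 44%, 80% power, alpha 0.05. The usual two-sided formula per arm is [1.96√(2p̄(1−p̄)) + 0.842√(p₁q₁+p₂q₂)]² / (p₁−p₂)². With p̄ = 0.52 it gives 152 per arm, or N = 304. The article attributes its figures to simulations with adherence and retention, so the gap to 314 shows no error. At N = 300 the formula gives 79.5% power.

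An exact 25% reduction is 0.75 × 60% = 45%. Then, with 150 per arm, z = (0.15 × √150 − 1.96 × √(2 × 0.525 × 0.475)) / √(0.24 + 0.2475) = (1.837 − 1.384)/0.698 = 0.649, which is 74.2% power. Summing the binomial probabilities exactly for the uncorrected chi-squared test gives 75.9%, so simulated values near 0.76 are the right reference.

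**2. Distance to the threshold.** 400 − 350 = 50 and 650 − 350 = 300 cells.

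**3. Spread of decline.** The sample size section gives a mean yearly decline of 114 (32-229) and says that 54% decline by more than 100, where CD4 evaluations are rare. The bracket is not labelled.

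- From the 54%, under a normal distribution: SD = (114 − 100)/0.1004 ≈ 139.
- Bracket read as an interquartile range: lower SD (114 − 32)/0.6745 ≈ 122, upper SD (229 − 114)/0.6745 ≈ 170. This gives Φ(14/122) ≈ 55% declining by more than 100, close to the stated 54%.
- Bracket read as a 95% range: SD = (229 − 32)/3.92 ≈ 50. This gives Φ(14/50) ≈ 61%, which does not fit the 54%.

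An SD of about 140 is therefore taken as the working assumption.

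**4. Risk gradient** (interquartile reading). P(decline > 50) = Φ(64/122) ≈ 70%. P(decline > 300) = 1 − Φ(186/170) ≈ 14%.

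**5. Power with and without baseline CD4.** Simulated with N = 300, 1:1 allocation, a one-year binary outcome driven by CD4 alone, and decline shifted to give 60% and 45% events. Entry CD4 is either uniform over 400-650 or skewed to the low end. The unadjusted chi-squared test is compared with a logistic model that includes baseline CD4.

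| SD of decline | Entry CD4 | Unadjusted | Adjusted |
|---|---|---|---|
| 140 | uniform | 0.767 | 0.807 |
| 140 | low-skewed | 0.759 | 0.772 |
| 150 | uniform | 0.757 | 0.807 |
| 150 | low-skewed | 0.746 | 0.758 |
| 100 | uniform | 0.776 | 0.859 |
| 100 | low-skewed | 0.768 | 0.835 |
| 50 | uniform | 0.754 | 0.972 |
| 50 | low-skewed | 0.775 | 0.943 |

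The SD 140 rows used 3,000 replicates. The other rows used 1,200, with Monte Carlo error of about 1 point, and a standardised risk difference from the logistic model. At SD 150 the variance of that difference falls to 0.876 (uniform) or 0.901 (low-skewed) of the unadjusted value, equivalent to 300/0.876 ≈ 342 or 300/0.901 ≈ 333 unadjusted patients. With no treatment effect (uniform entry, SD 100), the rejection rate was 0.0525 unadjusted and 0.052 adjusted.

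**6. Site.** A site-stratified test was compared with the unadjusted chi-squared test, with randomisation within two sites. For site event-rate gaps of 0, 10 and 20 points, power was the same for both (0.757, 0.757, 0.762). At a 30-point gap it went from 0.767 to 0.781, and the type I error of the unadjusted test was 0.039 against 0.050.

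**The case against.** The strongest reply is that nothing planned is invalid. An unadjusted randomised comparison is unbiased, and its type I error already allows for chance imbalance. The adjusted models are meant to explore baseline characteristics, so adding CD4 to that list alone would leave the primary p-value unchanged. All of this stands, and it is why the remedy has to reach the primary comparison. A covariate in a logistic or hazard model would also change the effect measure from a marginal risk ratio to a conditional ratio unless the result is standardised. That stands too and is met in the fix.

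Three stronger readings are tempting, and the documents do not support them.

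- **A double-digit power gain.** A reader might infer this from the SD 50 rows. They need a spread that conflicts with the 54% figure. Low-skewed entry, which the sample size section suggests by expecting high-CD4 patients to be rarer, shrinks the gain further.
- **Site as an equal source of lost precision.** Site matters only if event rates differ greatly between the two sites. The article reports no such difference, and only the abstract states randomisation by site.
- **Viral load as a needed covariate.** The article gives nothing from which its prognostic value could be sized.

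The article is also condensed. That would excuse a missing list, but not one that is given and omits this variable.

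**Conclusion.** The point holds as an efficiency improvement, not as a flaw in validity. Neither the main tests nor the named covariates use baseline CD4, the one measured variable that by design fixes how far each patient is from the main component of the primary outcome. At 300 patients and 60% versus 45%, using it is worth roughly 1 to 5 points of power, from about 0.76 to 0.77-0.81.

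That size rests on assumptions that the documents do not settle: an SD of yearly decline near 140, uniform or low-skewed entry CD4, 1:1 allocation, and a one-year outcome determined by CD4 alone. ART starts or AIDS illnesses less tied to entry CD4, and measurement error in CD4, would reduce the gain. Less variable decline would enlarge it. A reader might infer that the unadjusted result would be biased or its error rate inflated; neither is so.

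**What to change.** In the Analysis Plan section, pre-specify continuous baseline CD4 as a covariate in the primary comparison, and report a standardised (marginal) risk ratio with its 95% confidence interval so that the planned effect measure is kept. Include site as a stratum in the same analysis, and make the Randomization section agree with the abstract that blocks are formed within each site. The site term is there for consistency with the design.

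Keep age, gender and nutritional status for the secondary adjusted model. Baseline viral load may be added but is optional. The unadjusted comparison can stay as a supporting result.

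The cost is a few lines of wording, slight extra analysis work and reliance on a simple outcome model. No further data collection is needed.
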